### Blinding

Both the investigator and the subject will be blinded regarding the assignment of the study drugs. The contract research organisation (CRO; Kyung Hee University, Center for Clinical Research and Genomics) of the sponsor will label the investigational drugs by the randomisation code number. The labelled experimental products will be provided to the trial sites by the CRO.

### Recruitment

Participants will be recruited through posted notes on the bulletin boards at four hospitals: Catholic University of Korea Seoul St Mary's Hospital (located in Seoul, South Korea), Dongguk University Ilsan Oriental Hospital, Kyungwon Gil Oriental Medical Hospital (Ilsan and Incheon, South Korea, both satellite cities near Seoul) and Semyung University Oriental Medicine Hospital (Chungju, a midsized city located in central South Korea).

### Study schedule

The measurements that need to be carried out at each visit are listed in Table 4.

**Table 4 T4:** Study schedule of TJ001 clinical trial (12 weeks)^a^

	Initial screening b		Treatment period		
	
Measurement items	Visit 1 (-7 days)	Visit 2, week 0 (0 days)	Visit 3, 4 weeks (28 days)	Visit 4, 8 weeks (56 days)	Visit 5, 12 weeks (84 days)
Informed consent	Yes				
Demographic characteristics^c^	Yes				
Vital signs^d^	Yes	Yes	Yes	Yes	Yes
Medical/drug use history	Yes				
Smoking/drinking status	Yes		Yes	Yes	Yes
Physical examination^e^	Yes	Yes	Yes	Yes	Yes
Laboratory tests^f^	Yes				Yes
Thyroid hormones^g^	Yes				
Lipid test, CRP level^h^		Yes			Yes
Abdominal computed tomography for body fat		Yes			Yes
Blood sample for genetic test		Yes			
Electrocardiography	Yes				
Pregnancy test	Yes			Yes	Yes
Inclusion/exclusion criteria check		Yes			
Dietary intake measurement^i^		Yes	Yes	Yes	Yes
Concomitant medication		Yes	Yes	Yes	Yes
Adverse event			Yes	Yes	Yes
Questionnaires^j^		Yes			Yes
Questionnaire for Sasang					
Constitution Classification	Yes				
II					
Exterior Cold					
Disease induced from the		Yes	Yes	Yes	Yes
Esophagus affected by					
Cold' questionnaire in Tae-Eum-In persons Compliance calculation			Yes	Yes	Yes

^a^*CRP *C-reactive protein. ^b^The initial screening is performed within 1 week of the start of the study period. The visit windows for each participant are ± 3 days. ^c^Sex, date of birth, age, contact address and telephone number. ^d^Blood pressure (mmHg), pulse (beats/minute) and body temperature (°C). ^e^Body weight (kg), height (cm), waist circumference (cm) and hip circumference (cm). ^f^Blood tests are performed for haemoglobin, hematocrit, red blood cell count, white blood cell count, platelet count, total protein, albumin, total bilirubin, alanine transaminase, aspartate transaminase, alkaline γ-glutamyltransferase, uric acid, blood urea nitrogen/creatinine ratio, fasting plasma glucose, creatinine kinase and urine test for colour, specific gravity, pH, protein, glucose, ketone, urobilinogen, bilirubin, nitrite, red blood cells and white blood cells. ^g^Thyroid-stimulating hormone and free thyroxine are measured at the time of screening. ^h^Total cholesterol (mg/dl), high-density lipoprotein cholesterol (mg/dl), triglyceride (mg/dl) and CRP. ^i^Recorded in kilocalories using 24-hour dietary recall methods by a dietician or clinical research coordinator. ^j^Korean obesity-related quality of life (KOQOL) scale and Korean version of Eating Attitudes Test-26 (KEAT-26).

### Measurement tools

#### Anthropometric measuring for height, weight, waist circumference and hip circumference

All measurements will be taken by well-trained examiners using standard procedures. Measurements will be made while participants are dressed in light garments and with bare feet. Height and weight will be measured in the standing position to the nearest 0.1 cm and 0.1 kg, respectively. A measuring rod with a movable headpiece will be mounted on a balance beam scale. The waist circumference (WC), recorded to the nearest 0.1 cm, will be measured midway between the lower margin of the last rib and the top of the pelvic bone in a horizontal plane using plastic tape. The hip circumference (HC), recorded to the nearest 0.1 cm, will be measured at the horizontal level of the widest part of the hip. BMI is calculated by dividing weight in kilograms by height in square meters [29]. We will record the subjects' weight loss in kilograms at every visit and calculate BMI and the rate of monthly weight loss in both groups [30].

#### Questionnaires

##### Questionnaire for the Sasang Constitution Classification II

The Questionnaire for the Sasang Constitution Classification II Sasang Constitution Classification II classifies a person into one of four types of constitution according to personal traits based on I Je-ma's Sasang constitutional medicine theory [31]. We will use this questionnaire to classify obese Korean adults. Additionally, we will use this questionnaire to evaluate whether there is an association between each constitutional type and the effect of TJ001.

##### Exterior Cold Disease induced from the Oesophagus affected by Cold questionnaire in Tae-Eum persons

Exterior Cold Disease induced from the Esophagus affected by Cold questionnaire is used to evaluate symptoms that can occur in people of the Tae-Eum constitutional type according to the Sasang constitutional medicine theory [8]. We will apply this questionnaire to examine whether there is a relationship between the tendency toward obesity in Tae-Eum persons and their response to TJ001.

##### Compliance

All subjects will be asked to return the remaining investigational products at their next visit, and the rate of compliance (percentage) will be calculated on the basis of the returned products.

$$\text{Compliance}\left(\%\right)=\text{1}00-\text{returned}\;\text{products}/\text{expected}\;\text{intake}\times \text{1}00.$$

Investigational drugs will be distributed in packs of 100 at each visit.

100=3times/day×7days/week×4weeks/visit+16extras.

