#### Subject withdrawal criteria

The subjects who meet the criteria listed in Table 2 will be discontinued from treatment. The participants who will be withdrawn after randomisation will be followed for outcomes.

**Table 2 T2:** Subject withdrawal criteria

Subject withdrawal criteria
1. Protocol violation: detection of eligibility violations, poor compliance (mean compliance < 70% at the last estimation) or noncompliance, use of any forbidden medication or treatment during the trial that could affect the study results, occurrence of other significant protocol violation during the trial
2. Occurrence of a serious adverse event
3. Subject has an acute reaction (allergy, shock and so on) to the investigational product
4. Detection of a systemic disease that was not discovered at the screening stage
5. Unable to progress because of worsening of preexisting disease
6. Subject's withdrawal of consent
7. Subject is uncooperative
8. Investigator's decision to terminate the process for the sake of the subject's health

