### Interventions

Participating subjects assigned to either the treatment group or the placebo group will be instructed to take 7 g of TJ001 or placebo three times daily (a total of 21 g) for 12 weeks (84 days). TJ001 (Taeumjowi-tang granule extract, HANPOONG Pharm & Foods Co Ltd) is a compound of the powdered extract of several medicinal herbs, and the placebo will be similar to TJ001 in form, colour and odour. The components of TJ001 and the placebo are listed in Table 3.

**Table 3 T3:** Constituents of interventions (TJ001 and placebo)^a^

	**TJ001 granule extract**^**b**^		
**Name of herb**	**Raw material code**	**Dose (g)**	**Content (%)**

*Semen Coicis*	M040487	3.75	NA
*Semen Castaneae*	M089646	3.75	NA
*Semen Raphani*	M210181	2.5	NA
*Schisandrae Fructus*	M040445	1.25	NA
*Liriopis tuber*	M040139	1.25	NA
*Herba Ephedrae*	M040135	1.25	NA
*Radix platycodi*	M040048	1.25	NA
*Acori Tatarinowii Rhizoma*	M051377	1.25	NA

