### Statistical analysis

#### Efficacy assessment

The primary outcome will be analysed using the intention-to-treat (ITT) method. The secondary outcomes will be assessed by both the ITT and the per-protocol (PP) methods. The full analysis set for ITT method will include all randomised subjects, regardless of their subsequent withdrawal after enrolment. The PP analysis will include patients who have completed the 12-week study term without any major protocol violations and have a compliance rate > 70%. Missing values will be replaced by using the last observation carried forward method. Continuous variables will be reported as means ± SD, and categorical variables will be reported as percentages. The baseline characteristics will be compared by either Student's *t*-test for continuous variables or the χ^2 ^test (Fisher's exact test when the expected value is < 5) for categorical data. Alternatively, McNemar's test will be used if the normality assumption is not satisfied for the continuous variables.

For the within-group analyses, primary and secondary outcome variables will be evaluated by using a paired *t*-test. Alternatively, for nonnormal distribution data, the Wilcoxon test will be performed. Analysis of covariance will be applied to analyse differences in each group at every visit, adjusting for age, baseline weight and BMI as covariates. Between-group comparisons for each variable will be performed using Student's *t*-test. Statistical significance will be defined as *P *< 0.05. PASW for Windows version 18.0 software (SPSS, Inc, Chicago, IL, USA) will be used for the analyses.

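### The compliance formula counts the 16 extra dose units as missed doses, so full intake over 28 days scores 81% and a score of 70% means about 89% of doses taken

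*Protocol article*

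**What the plan says.** The Compliance section of the protocol article fixes three things.

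- **Returns.** "All subjects will be asked to return the remaining investigational products at their next visit".
- **Score.** Compliance is 100 minus the ratio of returned products to expected intake, times 100, so that "the rate of compliance (percentage) will be calculated on the basis of the returned products".
- **Supply.** "Investigational drugs will be distributed in packs of 100 at each visit", broken down as "100=3times/day×7days/week×4weeks/visit+16extras".

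The schedule behind the 84 is in Interventions: "three times daily (a total of 21 g) for 12 weeks (84 days".

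The score is then used twice. In Table 2 (Subject withdrawal criteria), item 1 lists "poor compliance (mean compliance < 70% at the last estimation") among the reasons for discontinuing treatment. Under Efficacy assessment, the per-protocol set is limited to subjects who complete the 12 weeks without major violations and "have a compliance rate > 70" per cent.

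**The concern.** A returned-product formula of this form measures intake correctly only if the amount dispensed equals the amount expected to be taken. The line after the formula shows that it does not. The supply exceeds the scheduled doses by 16 units. Those units sit in the returned count but not in the denominator, so a subject is marked down for not using product that was never meant to be used. Full marks go only to someone who returns nothing.

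The score is operational. It decides who is in the per-protocol set and is one trigger for stopping treatment. If it understates intake, the 70% figure in both rules acts on a different level of intake from the one that a reader would take it to mean. The per-protocol set can be rebuilt later, but a discontinuation made on a wrong score cannot be reversed.

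**Working it through.** **Inputs (all from the protocol article).** Three doses daily and 4-week intervals (Interventions; Compliance); 100 units dispensed per visit and the formula (Compliance); visit window ±3 days (footnote to Table 4); cut-offs of 70% (Table 2; Efficacy assessment).

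**The article's own figure.** 3 × 7 × 4 = 84 scheduled doses, and 84 + 16 = 100. The dispensing count reproduces.

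**Score over a nominal 28-day interval.** With *T* doses taken, 100 − *T* units come back, so score = 100 − (100 − *T*)/84 × 100.

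| Doses taken | True intake | Returned | Score as written |
|---|---|---|---|
| 84 | 100% | 16 | 80.95% |
| 75 | 89.3% | 25 | 70.2% |
| 74 | 88.1% | 26 | 69.0% |
| 58.8 | 70% | 41.2 | 51.0% |
| 0 | 0% | 100 | −19.05% |
| 100 | 119% | 0 | 100% |

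**Where 70% acts.** A score of 70 needs 0.30 × 84 = 25.2 units returned, so 74.8 taken, and 74.8/84 = 89.05%. In whole doses, 75 passes and 74 fails.

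**Pooling over the trial does not remove the offset.** Three intervals give 3 × 16 = 48 extras against 3 × 84 = 252 scheduled doses. 100 − 48/252 × 100 = 80.95%, as before.

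**Using 100 as the denominator does not rescue it.** Full intake then scores 100 − 16 = 84%, and a score of 70 means 70 doses taken, 70/84 = 83.3%.

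**Effect of the visit window on full intake.**

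- 25 days: 75 doses taken, 25 returned. With expected intake fixed at 84, 100 − 25/84 × 100 = 70.2%. With expected intake following the days, 100 − 25/75 × 100 = 66.7%.
- 31 days: 93 taken, 7 returned. Fixed at 84, 91.7%; day-based, 100 − 7/93 × 100 = 92.5%.

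**Lowest mean score for full intake with every visit inside its window.**

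- Visit 4, intervals of 31 and 22 days. Day-based: (92.5 + 48.5)/2 = 70.5%. Fixed at 84: (91.7 + 59.5)/2 = 75.6%.
- Visit 5, intervals of 25, 34 and 22 days. The 34-day interval needs 102 doses but only 100 are supplied, so none are returned and it scores 100. Day-based: (66.7 + 100 + 48.5)/3 = 71.7%. Fixed at 84: (70.2 + 100 + 59.5)/3 = 76.6%.

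**Check of the corrected measure.** (100 − returned)/84 × 100 gives (100 − 16)/84 × 100 = 100% for full intake, and a score of 70 falls at 58.8 of 84 doses, a true 70%.

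**The case against.** The strongest defence is that sites would net out the extras as a matter of course, and that a journal article condenses its protocol. Netting out would indeed remove the problem, but the article does not state it. What is at issue is also not an omission: the article prints an explicit formula next to an explicit supply count, and the two disagree. If netting is intended, the printed formula needs the same correction.

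Three stronger readings are tempting, and the document does not support them.

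- *Every score is 19 points too low.* This is exact only for a 28-day interval. For full intake the shortfall is 33.3 or 29.8 points at 25 days, and 7.5 or 8.3 at 31 days (day-based or fixed denominator).
- *A fully compliant subject meets the discontinuation rule.* Table 2 uses mean compliance below 70%. Full intake breaches that only at visit 3, only when the visit is exactly 3 days early, and only with day-based expected intake. At visits 4 and 5 the lowest means stay above 70%.
- *The primary result is biased or diluted.* The primary outcome is analysed by intention to treat in all randomised subjects, and withdrawn subjects are followed for outcomes. Lost exposure after a wrongful discontinuation could matter, but the document gives nothing from which to size it.

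The timing in Table 2 is also open. If the last estimation means the final one at week 12, no treatment is left to stop, and the consequence narrows to the per-protocol set.

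**Conclusion.** The formula is wrong as written. Over a nominal 28-day interval it scores full intake at 81%, scores no intake at −19%, and places a score of 70% at about 89% of doses taken. Subjects whose true intake lies between 70% and about 89% (59 to 74 of 84 doses) would fall outside the per-protocol set and could meet the discontinuation criterion.

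This rests on reading the Compliance section literally: all remaining units, including the extras, are in the returned count, and expected intake is the scheduled 84. The size of the offset depends on the visit interval and on whether expected intake follows the actual days, which the article does not say.

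The reach is limited. Per-protocol analysis is planned for secondary outcomes only, the primary analysis set is unchanged, and the number of subjects affected is unknown because no adherence distribution is given. No view is taken here on what the cut-off should be.

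**What to change.** Replace the formula with: compliance (%) = (units dispensed − units returned) / expected intake × 100. Subtracting the 16 extras from the returned count gives the same result when expected intake is fixed at 84. If it follows actual days, the quantity to subtract is units dispensed minus expected intake.

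State whether expected intake is fixed or follows the days between visits. Reconcile the Compliance section, Table 2 item 1 and the per-protocol definition under Efficacy assessment, so that all refer to the corrected measure, and say in Table 2 when the last estimation takes place.

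Recompute compliance from the pack counts already collected before the per-protocol set is built. Recalculation cannot restore treatment to anyone already discontinued on the old score.

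The cost is one line for the formula, short clarifying wording and a recalculation. No new data are needed.

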### Outcomes

Both primary and secondary end points will be measured at each visit according to the study schedule (Table 4).

#### Primary outcome

The primary outcome is the rate of subjects who have lost 5% or more of their baseline body weight [28,30,32].

#### Secondary outcomes

Both within-group and between-group analyses will be performed for each outcome. The differences in the following variables between the baseline (visit 1) and the last visit (visit 5) will be calculated.

• Body weight (kg)

• BMI (kg/m^2^)

• WC (cm)

• HC (cm)

• Waist/hip circumference ratio (WHR) change

Lipid profile: total cholesterol, triglyceride, HDL cholesterol, LDL cholesterol levels (mg/dl) (LDL cholesterol will be estimated using the Friedewald equation [33].)

Body fat composition: visceral fat area (cm^2^) and subcutaneous fat area (cm^2^) (Body composition will be evaluated by abdominal computed tomography.)

• Blood pressure (mmHg)

• Fasting plasma glucose concentration (mg/dl)

• C-reactive protein (mg/L) Questionnaires scores: Korean Obesity-related Quality of Life (KOQOL) and Korean version of Eating Attitudes Test-26 (KEAT-26)

#### Safety outcomes

All variables related to the safety assessment such as vital signs, general physical examinations, various test results (hematologic tests, biochemical tests, and urine tests) and adverse events (AEs) will be documented on the case report form (CRF) at every visit.

### Statistical analysis

#### Efficacy assessment

The primary outcome will be analysed using the intention-to-treat (ITT) method. The secondary outcomes will be assessed by both the ITT and the per-protocol (PP) methods. The full analysis set for ITT method will include all randomised subjects, regardless of their subsequent withdrawal after enrolment. The PP analysis will include patients who have completed the 12-week study term without any major protocol violations and have a compliance rate > 70%. Missing values will be replaced by using the last observation carried forward method. Continuous variables will be reported as means ± SD, and categorical variables will be reported as percentages. The baseline characteristics will be compared by either Student's *t*-test for continuous variables or the χ^2 ^test (Fisher's exact test when the expected value is < 5) for categorical data. Alternatively, McNemar's test will be used if the normality assumption is not satisfied for the continuous variables.

For the within-group analyses, primary and secondary outcome variables will be evaluated by using a paired *t*-test. Alternatively, for nonnormal distribution data, the Wilcoxon test will be performed. Analysis of covariance will be applied to analyse differences in each group at every visit, adjusting for age, baseline weight and BMI as covariates. Between-group comparisons for each variable will be performed using Student's *t*-test. Statistical significance will be defined as *P *< 0.05. PASW for Windows version 18.0 software (SPSS, Inc, Chicago, IL, USA) will be used for the analyses.

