**Methods:**

Our study is a randomised, double-blind, placebo-controlled, multicentre clinical trial of Taeumjowi-tang (TJ001). For this study, we will recruit obese Korean patients of both sexes, ages 18 to 65 years, from four university hospitals. A total of 104 subjects will be recruited. The participants will receive either 7 g of TJ001 or a placebo three times daily for 12 weeks. The primary end point will be the rate of subjects who lose at least 5% of their baseline body weight. The secondary end points will be changes in body weight, body mass index, waist circumference, hip circumference, waist/hip circumference ratio, lipid profiles, body fat composition, blood pressure, fasting glucose concentration, C-reactive protein and questionnaires related to the quality of life. The outcomes will be measured every 4 weeks. The study period will be 12 weeks and will include a total of five visits with each subject (at screening and at 0, 4, 8 and 12 weeks).

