### Sample size calculation

A sample size of 104 subjects was estimated for 80% power at a significance level of 0.05 and an attrition rate of 20%. Participants will be selected according to the eligibility criteria.

No preliminary studies of TJ001 were available to aid in estimating the percentage of subjects with 5% or greater weight loss [21]. Therefore, we set the rate at 40% for the TJ001 group and 13% for the placebo group on the basis of a reference paper [28]. The formula for calculating the sample size when allocating subjects at a ratio of 1:1 (TJ001:placebo) is as follows:

$$\begin{array}{c} n=\frac{{\left\{z_{1-\alpha }\sqrt{2\bar{p}\left(1-\bar{p}\right)}+z_{1-\beta }\sqrt{p_{t}\left(1-p_{t}\right)+p_{c}\left(1-p_{c}\right)}\right\}}^{2}}{{\left(p_{t}-p_{c}\right)}^{2}}\\ \;=\frac{{\left\{1.96\sqrt{2\left(0.265\right)\left(0.735\right)}+0.84\sqrt{\left(0.40\right)\left(0.735\right)+\left(0.13\right)\left(0.87\right)}\right\}}^{2}}{{\left(0.40-0.13\right)}^{2}}\approx 41 \end{array}$$

p_t_

The 5% or greater responder rate of the initial weight in TJ001 group = 40%.

p_c_

The 5% or greater responder rate of the initial weight in the placebo group = 13%.

$$\bar{p}:\left(p_{t}+p_{c}\right)/2=26.5\%\;z_{1-\alpha /2}=1.96,\;z_{1-\beta }=0.84$$

Allowing for an attrition rate of 20%, the number of subjects in each group is 52.

$$n^{*}=\frac{n}{\left(1-0.2\right)}=51.25\approx 52$$

Therefore, a total of 104 subjects are needed for this trial.

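### Last observation carried forward, the only stated rule for missing values, sets change to exactly zero for outcomes measured twice and makes the primary responder rate depend on when subjects leave

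*Protocol article*

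**What the plan says.** The Efficacy assessment section of the protocol article gives one rule: "Missing values will be replaced by using the last observation carried forward method". It is not limited by outcome, visit or reason for missingness. The same section defines the analysis set: "The full analysis set for ITT method will include all randomised subjects, regardless of their subsequent withdrawal after enrolment". Any missing value in that set is therefore filled by this rule.

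The primary endpoint is binary: "The primary outcome is the rate of subjects who have lost 5% or more of their baseline body weight". That sentence names no visit; week 12 is inferred from the 12-week treatment period and visit 5. Table 4 and its footnotes schedule body weight at all five visits. They schedule "Abdominal computed tomography for body fat", lipids, CRP and the KOQOL and KEAT-26 questionnaires only at weeks 0 and 12. Fasting glucose, part of the laboratory tests, is scheduled only at screening and week 12. The Secondary outcomes section defines each of these as a change from baseline to visit 5.

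Two further statements bear on how much will be missing. The Sample size calculation section says: "Allowing for an attrition rate of 20%, the number of subjects in each group is 52". The Subject withdrawal criteria section says: "The participants who will be withdrawn after randomisation will be followed for outcomes".

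**The concern.** For an outcome measured once before treatment and once at the end, the only value that can be carried forward is the pre-treatment one. The rule then amounts to baseline carried forward: each missing subject enters the analysis with a change of zero, treated as an observation. This pulls the estimated difference towards zero when dropout is equal, can create a difference when dropout is unequal, and makes the spread of the data look smaller than it is.

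For the primary outcome, a subject with no week-12 weight is classified on an earlier one. Someone already 5% down at week 4 or 8 counts as a responder, as if the loss had lasted. Someone not yet at 5% counts as a non-responder. The responder rate therefore depends partly on when people leave.

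This matters here because the stated objectives include producing estimates of obesity-related variables and choosing an endpoint and treatment period, to guide a larger trial. Distorted rates, differences and SDs would be carried into that design.

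**Working it through.** **The plan's own figure.** Inputs from the Sample size calculation section: 40% v 13% responders, z values 1.96 and 0.84, 20% attrition. With p_t(1 − p_t) = 0.40 × 0.60, the formula gives 40.7, rounded up to 41 per arm; 41/0.8 = 51.25, rounded up to 52 per arm and 104 in total. The stated size reproduces. (The printed substitution has 0.40 × 0.735 in that term, a separate slip that would give 42.5.) The expected number lost is 0.20 × 52 = 10.4 per arm, or 20.8 in total.

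**Outcomes measured twice.** Let d be the share missing in each arm. Let change have SD 1 and arm mean m, with dropout unrelated to the change.
- Mean after zero-filling: (1 − d)m. At d = 0.20, a true difference of 0.50 SD becomes 0.8 × 0.50 = 0.40 SD. At d = 10% and 30% it becomes 0.45 and 0.35 SD.
- Variance after zero-filling: (1 − d) + d(1 − d)m², which is 0.8 + 0.16m² at d = 0.20.
- Ratio of the zero-filled SE (52 per arm) to the completers' SE (41.6 per arm): √(0.8 × average variance of the two arms).
  - Both arm means 0: √(0.8 × 0.80) = 0.80.
  - Arm means −0.5 and 0: √(0.8 × 0.82) = 0.81.
  - Arm means −1.0 and −0.5: √(0.8 × 0.90) = 0.85.
- Coverage for arm means −0.5 and 0: the bias is 0.10 and the SE is √(1.64/52) = 0.178, so the shift is 0.56 SE. A nominal 95% interval would cover the true difference about 91% of the time.
- Unequal dropout of 10% v 30%, with the same true change of −0.5 SD in both arms: the zero-filled means are −0.45 and −0.35, a spurious difference of 0.10 SD. Rejection is then about 9% instead of 5%.

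**Primary outcome.** The documents do not say how many dropouts will have reached 5% at their last visit, so those shares (q) are assumptions. With completers at 40% v 13% and 20% missing per arm, the analysed rate is 0.8p + 0.2q. Power uses the plan's pooled-variance approach at 52 per arm.

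| Missing subjects past 5% (TJ001 / placebo) | Analysed rates | Difference (points) | Power |
|---|---|---|---|
| 0 / 0 (same as non-response) | 32.0% v 10.4% | 21.6 | 77.7% |
| 20% / 6.5% | 36.0% v 11.7% | 24.3 | 83.9% |
| 40% / 13% | 40.0% v 13.0% | 27.0 | 88.8% |
| 40% / 0 | 40.0% v 10.4% | 29.6 | 94.7% |
| 0 / 13% | 32.0% v 13.0% | 19.0 | 64.4% |

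With identical completers, the analysed difference runs from 19.0 to 29.6 points around the planned 27.

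If both arms truly have 13% responders at week 12, the effect on type I error also depends on q. With 40% of missing TJ001 subjects and 13% of missing placebo subjects past 5% when they left, the analysed rates are 18.4% v 13.0% and rejection is about 12%. If both shares are 13%, it stays at 5%.

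**The case against.** The strongest reply is that the rule fills only missing values, and the article plans to follow withdrawn subjects for outcomes. A week-12 weight measured after withdrawal is not missing. This stands. About 21 imputed outcomes is therefore a ceiling, and the rule applies mainly to subjects lost to follow-up or refusing all further contact.

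A reader might infer that the rule turns subjects who stop TJ001 for side effects into treatment successes, and so inflates the effect. The documents do not support that. Such subjects fall under the withdrawal criteria and should have a real week-12 weight, and the rule also scores as failures those who had not yet reached 5%. In the 20% / 6.5% scenario, where missing subjects respond at half the completers' rate, the analysed difference is 24.3 points. That is below the planned 27 and only 2.7 points from the non-response result.

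For outcomes measured twice, equal dropout does not make the test liberal. The estimate and its SE shrink almost together (0.80 against 0.80 to 0.85), so the test statistic is unchanged or slightly smaller. The article plans P values and means with SDs and mentions no confidence intervals, so the coverage figure shows the distortion rather than an error in a planned output. Secondary outcomes are also analysed per protocol in 12-week completers, so the zero-filled result would not stand alone. That set also excludes subjects for compliance and protocol violations, so it does not isolate the effect of missing data.

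Finally, counting missing weights as non-response also assumes no benefit, and it shrinks the planned difference by the same 20% (27 to 21.6 points). That is true, and unequal dropout would affect it too. Its advantage is that success must be shown at week 12, so the result does not depend on weights at earlier visits. The continuous outcomes have better alternatives to filling in a fixed number.

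**Conclusion.** The point holds as a weakness of a rule that the article states, not as a missing detail. It is firmest for lipids, CRP, CT fat areas, KOQOL, KEAT-26 and fasting glucose, where zero change follows directly from the schedule, provided that pre-treatment values may be carried forward. The unqualified rule and the all-randomised set imply that they may. At 20% missing in both arms, the mean difference is understated by 20% and the SE is about 0.80 to 0.85 of the completers'. With less missing data both effects are smaller.

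For the primary outcome, the conclusion is only that the result depends on dropout timing, in a direction and by an amount that cannot be known beforehand. The range of 19.0 to 29.6 points rests on assumed dropout patterns and on all 20% being missing. The sample size is not wrong on this account. However, it was built on 41 evaluable subjects per arm while the analysis uses all 52, so actual power depends on how the missing subjects are scored. The rule should be changed; it does not invalidate the trial.

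**What to change.** 1. State that the primary endpoint is assessed at week 12, and that week-12 weights observed after withdrawal are used and take precedence over any carried value.
2. Count a week-12 weight that is still missing as non-response in the primary analysis.
3. For continuous outcomes measured at several visits (weight, BMI, waist, hip and their ratio, blood pressure), use a likelihood-based repeated-measures model.
4. For outcomes measured twice, use a baseline-adjusted analysis with multiple imputation. Other principled methods would also serve for items 3 and 4.
5. Keep last observation carried forward as a sensitivity analysis.

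The cost is revised wording and modest programming. If all 20% were missing and counted as non-responders, primary power at 52 per arm would be about 78% (77.7%), against the stated 80%; reaching 80% in that worst case would take 56 per arm, 112 in total. Every week-12 weight recovered through the planned follow-up reduces this loss.

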### Study groups

The study will include the following two arms: the TJ001 group (treatment arm) and the placebo group (control arm).

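### McNemar's test cannot serve as the non-normal alternative for baseline continuous variables, and the between-group analysis of skewed secondary outcomes has only untransformed parametric methods

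*Protocol article*

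**What the plan says.** All the rules are in the protocol article, Statistical analysis, Efficacy assessment.

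- **Baseline.** "The baseline characteristics will be compared by either Student's *t*-test for continuous variables", with the chi-square or Fisher's exact test for categorical data. The next sentence, which closes that paragraph, adds that "McNemar's test will be used if the normality assumption is not satisfied for the continuous variables".
- **Outcomes within groups.** A new paragraph gives the paired t-test, then: "Alternatively, for nonnormal distribution data, the Wilcoxon test will be performed".
- **Outcomes, covariate-adjusted.** "Analysis of covariance will be applied to analyse differences in each group at every visit, adjusting for age, baseline weight and BMI as covariates".
- **Outcomes between groups.** "Between-group comparisons for each variable will be performed using Student's *t*-test". No alternative or transformation follows.

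The Study groups section sets up two parallel arms, TJ001 and placebo. The Secondary outcomes section asks for both within-group and between-group analyses of every listed variable, as differences between baseline and the last visit. The list includes triglycerides in mg/dl and CRP in mg/L.

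**The concern.** There are two separate defects.

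First, McNemar's test compares two proportions measured on the same or matched subjects. The sentence applies it to variables that are continuous rather than binary, in arms that are independent rather than paired. It fails on both counts, so the stated rule cannot be carried out.

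Second, the plan foresees non-normal data for the within-group analyses and provides a rank test there. For the randomised comparison it fixes the t-test for each variable and provides no such alternative. An analyst who finds a strongly skewed CRP change must either keep a raw-scale mean comparison that a few extreme values can dominate, or choose another method after seeing the data. This matters for a trial whose stated objectives include producing estimates of obesity-related variables to guide a larger study.

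**Working it through.** **1. McNemar's test, by reading.** The test needs pairs and a binary variable. The sentence supplies unpaired arms and continuous variables. No arithmetic is involved: there is no 2×2 table of paired outcomes to form.

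**2. Sample size, to fix n for the illustration.** With rates of 40% and 13%, mean 0.265, z = 1.96 and 0.84:

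n = {1.96·√(2 × 0.265 × 0.735) + 0.84·√(0.40 × 0.60 + 0.13 × 0.87)}² / 0.27² = 40.7, rounded up to 41.

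Then 41/0.8 = 51.25, rounded up to 52 per arm and 104 in total, as the article states. (The printed line shows 0.735 where 0.60 belongs in the TJ001 variance term. That is a separate matter, and the stated 41 follows from 0.60.) The article's full analysis set contains all randomised subjects with missing values carried forward, so 52 per arm is the relevant n.

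**3. What non-normality costs in the between-group comparison.** The article gives no distribution for CRP or triglycerides, so these inputs are assumptions:

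- log-normal values with log-SD s = 0.5, 1.0 or 1.2
- correlation of 0.6 between the logs of baseline and final value
- a treatment shift of 0.5·s on the log scale at the final visit, that is a ratio of exp(−0.25) = 0.78, exp(−0.5) = 0.61 or exp(−0.6) = 0.55
- two-sided 5% level

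The variable analysed is the change from baseline, as the Secondary outcomes section specifies.

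| Log-SD | t-test on raw change | Rank-sum on raw change | t-test on log ratio |
|---|---|---|---|
| 0.5 | 0.67 | 0.70 | 0.80 |
| 1.0 | 0.42 | 0.64 | 0.81 |
| 1.2 | 0.34 | 0.60 | 0.80 |

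These are simulated powers at 52 per arm. Repeat runs of 10,000 trials agree to within about two percentage points; for example, the rank-sum figure at log-SD 1.0 also came out at 0.62.

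The log-ratio column can be checked by hand. The standardised effect is 0.5/√(2 × (1 − 0.6)) = 0.559. The non-centrality is 0.559 × √(52/2) = 2.85. Power is about Φ(2.85 − 1.98) = Φ(0.87) = 0.81, whatever the log-SD.

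With 41 per arm the pattern is the same: raw t-test 0.56/0.35/0.28, rank-sum 0.60/0.51/0.51, log ratio 0.70/0.71/0.71.

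**4. Type I error.** With no treatment effect, the raw t-test on change rejected in 0.039 to 0.052 of runs across these settings. The error rate is not inflated.

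**The case against.** The strongest objection is to joining the two defects. A reader might infer that the McNemar error is what leaves skewed outcomes without a usable test. The text does not support this: the sentence ends the baseline paragraph, the outcome rules begin in the next one, and correcting the sentence alone would change no outcome analysis. The gap for outcomes comes from the separate t-test sentence.

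A reader might also infer that a raw-scale t-test is the only between-group analysis. That is too strong, because ANCOVA at every visit is also named. However, no transformation is stated for it, and its covariates are age, weight and BMI rather than the outcome's own baseline, so it is no alternative for skewed data. It was not simulated.

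Third, the skewness, the correlation and the effect size are all assumed. At log-SD 0.5 the rank-sum test gains only about 0.03 over the raw t-test. This limits how much weight the table can bear, but not the reading of the text.

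Finally, a transformation or rank test is detail often left to an analysis plan that is not shown. That would answer silence. Here the article names an inapplicable test and fixes the t-test for each variable, so both points concern what it states.

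**Conclusion.** The point holds in two parts. The McNemar rule is wrong as written and cannot be applied to the baseline comparison; this rests on the text alone. Separately, between-group comparisons of secondary outcomes rely only on untransformed parametric methods, with no alternative for non-normal data.

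The size of the second part depends on the assumed skewness. At log-SD 1.0 and 52 per arm, the raw t-test has power of about 0.42, against 0.64 for the rank-sum test and 0.81 for the log ratio.

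The documents and the check do not support a claim of false positives, since type I error stays near nominal. Nor do they support a claim that the main result is at risk: the primary outcome is a binary responder rate, and neither its comparison nor the sample size depends on these rules. This is a correction that should be made, at the level of baseline reporting and secondary outcomes.

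**What to change.** Three wording changes in the Efficacy assessment section:

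1. Replace McNemar's test with the Wilcoxon rank-sum (Mann-Whitney) test for non-normal continuous baseline variables.
2. Analyse CRP and triglycerides between groups on the log scale, adjusted for the outcome's own log baseline, and report the ratio of geometric means with its 95% confidence interval. Under the correlation assumed above, this adjustment would lower the residual variance from 2 × (1 − 0.6) = 0.80 to 1 − 0.6² = 0.64 of the log-scale variance, so it should do at least as well as the log-ratio column.
3. Name the rank-sum test as the between-group alternative for other non-normal secondary outcomes.

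The cost is a few sentences in the protocol or analysis plan, best fixed before unblinding. No data collection changes, and N stays at 104.
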